## Abstract

**Background::**

Many of the painful, disabling features of early diffuse cutaneous systemic
sclerosis have an inflammatory component and are potentially treatable with
corticosteroid therapy. These features include painful and itchy skin,
fatigue and musculoskeletal involvement. Yet many clinicians are
understandably reluctant to prescribe corticosteroids because of the concern
that these are a risk factor for scleroderma renal crisis. The aim of PRedSS
(PRednisolone in early diffuse cutaneous Systemic Sclerosis) is to evaluate
the efficacy and safety of moderate dose prednisolone in patients with early
diffuse cutaneous systemic sclerosis, specifically whether moderate dose
prednisolone is (a) effective in terms of reducing pain and disability, and
improving skin score and (b) safe, with particular reference to renal
function.

**Methods::**

PRedSS is a Phase II, multicentre, double-blind randomised controlled trial
which aims to recruit 72 patients with early diffuse cutaneous systemic
sclerosis. Patients are randomised to receive either prednisolone (dosage
approximately 0.3 mg/kg) or placebo therapy for 6 months. The two co-primary
outcome measures are the difference in mean Health Assessment Questionnaire
Disability Index at 3 months and the difference in modified Rodnan skin
score at 3 months. Secondary outcome measures include patient reported
outcome measures of itch, hand function, anxiety and depression, and
helplessness.

**Results::**

Recruitment commenced in December 2017 and after a slow start (due to delays
in opening centres) 25 patients have now been recruited.

**Conclusion::**

PRedSS should help to answer the question as to whether clinicians should or
should not prescribe prednisolone in early diffuse cutaneous systemic
sclerosis.

## Introduction

Diffuse cutaneous systemic sclerosis (dcSSc) is a potentially devastating illness
with a very major impact on quality of life as well as on survival. Affected
patients typically experience rapid progression of skin thickening, commencing
distally but going on to involve proximal limb and/or trunk, often with early
involvement of internal organs. Early dcSSc is characterised by pain, stiffness,
disability, disfigurement, fatigue, intractable itch and (often) a feeling of
helplessness. Currently, there is no cure. The major impact on quality of life in
patients with early dcSSc is in the context of a 10-year survival rate of little
more than 50%.^
1
^ Risk factors for death include extensive skin involvement, early internal
organ involvement (lung, heart and kidney) and anti-topoisomerase (anti-Scl70)
antibodies.^2,3^
Understandably, clinicians caring for patients with early dcSSc have therefore
tended to focus on early identification and treatment of internal organ involvement,
and on immunosuppressive therapy,^4,5^ on the basis that there is
evidence of immune activation with inflammation early in the disease
course.^6,7^
Although randomised controlled trials (RCTs)^8,9^ have shown that haemopoetic stem
cell transplantation (HSCT) confers survival advantage, these trials were in highly
selected patients, and HSCT tends to be reserved for those patients with the poorest
prognosis.

Focusing on the internal organ involvement of early dcSSc risks ignoring the aspects
of disease which have the most impact upon patients’ day-to-day lives, namely,
painful and itchy skin, fatigue and loss of function due to a combination of early
contractures (especially of the fingers) and musculoskeletal involvement. This
musculoskeletal involvement includes tendinitis, myositis and/or joint inflammation
which may be unrecognised. Many of these early features which severely impact on
quality of life have an inflammatory component and are potentially treatable with
steroid therapy. However, corticosteroids are much less frequently prescribed in
patients with systemic sclerosis (SSc) than in patients with other connective tissue
diseases. This is because (a) SSc is not generally considered primarily an
inflammatory disease (instead being characterised by fibrosis and ischaemia,
although as stated above, there is a degree of inflammation in early diffuse
disease) and (b) corticosteroids are a risk factor for renal crisis,^10–12^ which is most likely to occur
in that subset of patients with early diffuse cutaneous disease. Patients who are
anti-RNA polymerase III antibody positive are at particular risk of renal
crisis.^13,14^

Hence, there is a clinical dilemma: should corticosteroids be prescribed or
not?^7,15^ Anecdotally,
many clinicians with an interest in SSc prescribe low dose corticosteroids (e.g.
prednisolone 10 mg/day or less) and report that patients are symptomatically
improved. However, other clinicians will not prescribe corticosteroids because of
understandable concerns about adverse effects (hypertension, renal crisis), although
open-label studies in patients with early dcSSc including low to medium dose
corticosteroids did not report renal crises^16–18^ and several other studies in
patients with SSc in which treatment regimens have included steroid therapy have not
reported adverse renal outcomes (reviewed in 15). The difference in opinion as to
whether steroids should or should not be prescribed in early dcSSc was recently well
illustrated by experience from the European Scleroderma Observational Study (ESOS)^
19
^: of 326 patients recruited, 141 (44%) reported current or previous
corticosteroid use. A meta-analysis published in 2014 also reported a high
prevalence of corticosteroid use in patients with dcSSc.^
20
^

Against this background, our overall hypothesis is that moderate dose prednisolone
confers symptomatic and functional benefit in patients with early dcSSc and that the
benefit outweighs any side effects. This hypothesis relates specifically to patients
with early diffuse (as opposed to limited) cutaneous SSc. The main benefits are
expected through anti-inflammatory effects in the skin and in the musculoskeletal
system, thus preventing late and irreversible complications including finger
contractures (Figure 1).
Therefore, the overall aim of ‘PRednisolone in early diffuse cutaneous Systemic
Sclerosis’ (PRedSS) is to evaluate the efficacy and safety of moderate dose
prednisolone in early dcSSc. Specific objectives are to evaluate whether

Moderate dose prednisolone is effective in patients with early dcSSc in terms
of reducing pain and disability and improving skin score.Moderate dose prednisolone is a safe therapy in patients with early dcSSc
(with particular reference to renal function).

**Figure 1. fig1-2397198320957552:**
[figure not shown]
Finger flexion contractures in a patient with established dcSSc.

## Methods

### Study design

PRedSS (ClinicalTrials.gov Identifier: NCT03708718) is a Phase II, multicentre,
double-blind RCT which will evaluate the efficacy and safety of moderate dose
prednisolone in 72 patients with early dcSSc over a 6-month period, with the
co-primary endpoints (see below) being assessed at 3 months. The decision to
have the primary endpoint at 3 (as opposed to 6) months was taken to maximise
patient retention in the study up until the primary endpoint. The study was
approved by the North West – Greater Manchester South Research Ethics Committee
on the 28 June 2017: all patients sign informed consent.

#### Randomisation

Eligible patients are randomised 1:1 to receive either enteric-coated
prednisolone or matching placebo capsules (1 active capsule = 5-mg
prednisolone) (Figure 2). Randomisation is stratified according to whether the patient
is positive for anti-topoisomerase antibody. Although ideally randomisation
would have been stratified for anti-RNA polymerase III positivity, this was
deemed too logistically difficult because not all participating centres have
rapid access to testing for anti-RNA polymerase III. Because
anti-topoisomerase antibody and anti-RNA polymerase III are almost
invariably mutually exclusive, it is likely that this chosen approach will
result in similar numbers of patients who are anti-RNA polymerase III
antibody positive being randomised to each of the two treatment groups.

**Figure 2. fig2-2397198320957552:**
[figure not shown]
Study design.

#### Treatment

The dosage schedules have been designed so that patients receive
approximately 0.3 mg/kg of prednisolone or less: weight <50 kg = 10 mg;
⩾50 kg but <60 kg = 15 mg; ⩾60 kg but <80 kg = 20 mg, ⩾80 kg but
<100 kg = 25 mg; ⩾100 kg = 30 mg. These doses were chosen because they
are thought to be high enough to be associated with substantial
anti-inflammatory effects, but at the same time not so high as to deter
clinicians concerned about the renal side effects thought to be associated
with high dose. If a patient experiences adverse effects deemed in the
opinion of the investigator to be likely related to trial treatment and to
warrant reducing the dose of prednisolone (or placebo equivalent), then the
dose may be reduced at the clinician’s discretion, and the reason recorded.
This trial treatment is additive to (and not a substitute for) any other
therapies which might be prescribed. For example, as described below under
inclusion and exclusion criteria, a patient on immunosuppressant therapy may
be entered into the trial. This reflects the ‘real-world’ situation post-RCT
if prednisolone is found to be effective: prednisolone will be prescribed in
addition to other therapies. A proton pump inhibitor, and a calcium and
vitamin D supplement, are co-prescribed with the trial treatment on the
basis that there is a 50% chance that this is prednisolone which may cause
upper gastro-intestinal side effects and which is a risk factor for
osteoporosis.

#### Visit schedule and study exit

Patients attend on five occasions (Figure 2): a screening visit (up to
28 days before the baseline visit), baseline, 6 weeks, 3 months and
6 months. At the 6-month (final) visit, the treatment code is broken,
because corticosteroid therapy cannot be stopped suddenly and it is
therefore important that both clinician and patient know whether the patient
is on prednisolone therapy. For those patients randomised to prednisolone,
the clinician then makes a decision as to whether or not to continue the
current dose, whether to reduce the dose or whether to gradually taper the
dose with a view to discontinuing.

The trial will complete when the last patient has completed the 6-month
visit. Any patients discontinuing treatment prior to their 6-month visit are
asked to attend all visits and complete all assessments as previously
intended.

### Patients

Inclusion and exclusion criteria are listed in Table 1.

**Table 1. table1-2397198320957552:** Inclusion and exclusion criteria.

Inclusion criteria	
a.	Aged 18 years or more
b.	DcSSc (with skin involvement extending to proximal limb and/or trunk)
c.	Skin involvement of less than 3 years
Exclusion criteria	
a.	Previous renal crisis or significant renal impairment (estimated glomerular filtration rate (GFR) < 40 mL/min)
b.	Currently on corticosteroid therapy, or previous corticosteroid therapy (with the exception of inhaled or topical steroids) within the last 4 weeks.
c.	Currently on an immunosuppressant (e.g. mycophenolate mofetil, methotrexate) or biologic therapy the dose of which has changed in the previous 4 weeks, or is likely to change during the first 3 months of trial treatment. Patients on immunosuppressant therapies should ideally remain on the same dose throughout the study period, although it is recognised that this may not be possible.
d.	Patients with significant uncontrolled Stage 1 hypertension (clinic BP >140/90 mmHg). Patients with previous hypertension which is controlled for at least 4 weeks are considered eligible.
e.	Any condition which in the opinion of the attending clinician would make corticosteroid therapy unwise (e.g. chronic infection, unstable diabetes, uncontrolled blood pressure).
f.	Patients with major myositis or inflammatory arthritis. Patients with low-level myositis or inflammatory arthritis are eligible for inclusion (e.g. in the case of myositis, a creatine kinase less than 4 times the upper limit of normal or myositis only demonstrable on magnetic resonance imaging).
g.	Female patients who are pregnant at time of screening.
h.	Female patients who are breastfeeding.
i.	Patients with significant inflammatory bowel disease as judged by the investigator.
j.	Patients currently participating in another randomised controlled trial.
k.	Patients who do not fully understand the importance of not suddenly stopping taking the study medication.

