#### Statistical analysis

Primary analyses will be conducted on an intention-to-treat basis; withdrawn
patients will continue to complete visits and their measurements will be
included in the analysis. The two co-primary outcome measures (HAQ-DI and
mRSS) will each be analysed as continuous variates using a Mixed Model for
Repeated Measures (MMRM) to assess any differences between the treatment
arms. Each model will include the fixed categorical effects of treatment
(i.e. prednisolone and placebo), time point (i.e. 6 weeks, 3 months and
6 months), whether a patient is anti-topoisomerase positive, baseline scores
as well as the interactions of all fixed terms by time point. This will
ensure the effects are permitted to vary for each of the three time points.
The models will also be adjusted for any baseline characteristics found to
be predictive of missing outcome values. A general unstructured covariance
matrix will be used (six parameters). The models will be fitted using
REstricted Maximum Likelihood (REML) and will employ Kenward and Roger
degrees of freedom adjustment. The primary focus will be the contrast
(adjusted mean difference) between treatment arms at 3 months.

There are a large number of secondary outcomes (listed in Table 2), and
these will be analysed in an analogous manner to the co-primary outcomes.
These analyses will be exploratory in nature each employing an unadjusted
2-tail 5% significance level for the trial arm comparison at 3 months.

Further exploratory analyses will compare the trial arms for the HAQ-DI, mRSS
and other secondary outcomes at the other time points, that is, 6 weeks and
6 months, respectively. A single interim futility analysis is planned after
approximately 30 participants have 3-month outcome data with early stopping
only permitted for lack of benefit in both co-primary outcomes.

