### Covid-19 impact

On 23/3/2020, the decision was taken to break the code for the 11 patients
currently on trial treatment, as it was felt inappropriate for patients and
their clinicians to remain blinded to which patients were receiving prednisolone
treatment during the pandemic. This was against the background of the British
Society for Rheumatology recommending that patients on both immunosuppressant
therapy and prednisolone should be ‘social shielding’ as per National Health
Service England guidance. Given that 10 of the 11 patients were on either
mycophenolate mofetil or methotrexate, it was therefore considered untenable to
maintain the double-blind. All 11 patients remained on trial on an open-label
basis. Recruitment was suspended until deemed safe to re-open. Ethics approval
has been obtained to convert PRedSS to a randomised open-label study, which is
now a preferable approach given that ongoing concerns regarding Covid-19 would
often make it difficult to maintain the double-blind.

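### Optional efficiency point: the primary models adjust for baseline score and anti-topoisomerase status but make no planned use of time since onset of skin involvement, forgoing perhaps 1 to 4 points of power

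*Protocol article*

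**What the plan says.** **Entry.** Table 1 (Patients), inclusion criterion c, is "Skin involvement of less than 3 years". Background immunosuppressants are allowed but not required: under Treatment, "a patient on immunosuppressant therapy may" be entered. Exclusion criterion c removes patients whose dose changed in the preceding 4 weeks or "is likely to change during the first 3 months of trial treatment".

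**Randomisation.** Allocation is 1:1 with one stratification factor: "Randomisation is stratified according to whether the patient" is anti-topoisomerase positive.

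**Primary models.** Under Statistical analysis, "Each model will include the fixed categorical effects of treatment", together with time point, anti-topoisomerase status and baseline score, each interacting with time point. The same section gives one rule for adding covariates: a baseline characteristic is added if it is found to predict missing outcome values.

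**Disease course.** The Introduction describes rapid skin progression as typical of the diffuse subtype and places immune activation and inflammation early in its course.

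**Conduct.** Under Covid-19 impact, the code was broken for the 11 patients then on trial treatment, and ethics approval was obtained to continue open label.

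**The concern.** The baseline score records how severe a patient's disease is at entry. It does not record how long the patient took to get there. Two patients with the same mRSS, one 3 months and one 33 months after skin onset, are exchangeable in the planned model unless they differ in antibody status. If duration predicts the 3-month score beyond baseline score and antibody status, that variation stays in the residual.

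The covariate rule does not close this gap, because it selects on missingness rather than prognosis. A strongly prognostic duration effect would be ignored if duration did not predict dropout. Conversely, duration could enter after the data are seen, for a reason unrelated to precision.

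What is at stake is a modest amount of precision in a trial planned on 60 evaluable patients.

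**Working it through.** **Inputs from the article (Sample size calculation).** 30 evaluable patients per arm; two-sided α = 0.025 for each co-primary outcome. HAQ-DI: SD 0.9, difference 0.6, baseline correlation r = 0.6. mRSS: SD 8.2, difference 5.5, r = 0.9, with r = 0.6 as the cautious case.

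**Step 1: reproduce the stated power.** Residual SD = SD × √(1 − r²); SE = residual SD × √(2/30); noncentral t with 57 df.

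| Outcome | Residual SD | SE | Difference/SE | Power | Stated |
|---|---|---|---|---|---|
| HAQ-DI, r = 0.6 | 0.9 × 0.8 = 0.72 | 0.186 | 3.23 | 82.0% | 82% |
| mRSS, r = 0.6 | 8.2 × 0.8 = 6.56 | 1.69 | 3.25 | 82.5% | 82% |
| mRSS, r = 0.9 | 8.2 × 0.436 = 3.57 | 0.92 | 5.96 | >99.9% | 99% |

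The stated figures are met with no duration term.

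**Step 2: add one covariate.** Let duration explain a further share R² of the residual variance. The article gives no value, so R² is an assumption. The residual SD is multiplied by √(1 − R²) and one degree of freedom is spent (56 df). The gain expressed as extra evaluable patients is 60 × (1/(1 − R²) − 1).

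| R² | HAQ-DI power | mRSS power, r = 0.6 | Equivalent extra patients |
|---|---|---|---|
| 0 | 81.9% | 82.4% | 0 |
| 0.03 | 83.2% | 83.7% | 1.9 |
| 0.05 | 84.0% | 84.5% | 3.2 |
| 0.10 | 86.1% | 86.5% | 6.7 |

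With R² = 0 the HAQ-DI loss is below 0.1 point (81.98% to 81.94%). For mRSS at r = 0.9, power stays above 99.9% throughout.

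**Step 3: chance imbalance.** If duration is uniform on 0 to 36 months (assumption), its SD is 36/√12 = 10.4 months. With 30 per arm, the arm difference in mean duration has SD 10.4 × √(2/30) = 2.7 months, so a 95% range of about ±5.3 months. An imbalance of 1.96 SD shifts the contrast by √R² × 1.96 × SE:

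- R² = 0.05: 0.22 × 1.96 × 0.186 = 0.08 HAQ-DI points, or 0.7 mRSS points (SE 1.69).
- R² = 0.10: 0.32 × 1.96 × 0.186 = 0.12 HAQ-DI points, or 1.0 mRSS points.

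Even the larger shift is about 0.6 of a standard error (1.96 × √0.10 = 0.62).

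**Step 4: type I error without the covariate.** In 20,000 simulated null trials of 30 per arm, with an omitted covariate explaining 10% or 20% of the variance, the rejection rate was 2.4% and 2.6% against a nominal 2.5%.

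**Step 5: immunosuppressant use.** The only usage figure is under Covid-19 impact: "Given that 10 of the 11 patients were on either" mycophenolate mofetil or methotrexate. At 10/11 use and 30 per arm, the probability that the arms differ by 20 percentage points or more is 1.4%; at 50% use it would be 15.5%. A nearly constant covariate can neither be badly unbalanced nor explain much variance.

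**The case against.** The strongest reply is that nothing here is wrong. The article pre-specifies a coherent model that adjusts for the baseline score and the stratification factor, and further prognostic covariates are commonly left to the analysis plan, which is not shown. That reply largely stands, which is why the point is optional; if the analysis plan already lists duration, it is met. What survives is that the article is not merely silent: it states a rule for extending the model, and that rule selects on missingness.

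Two further objections also have force. The article never says that patients at month 3 and month 33 change at different rates; prognostic value is a plausible reading of its account of early disease, not a documented fact. And the HAQ-DI correlation of 0.6 comes from one-year follow-up, so the 3-month correlation may differ and the baseline score may carry more or less than assumed.

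A reader might infer three stronger claims that the document does not support:

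- **That the primary contrast is biased.** Chance imbalance under randomisation is not bias in the estimator. The standard error already covers it, and the simulated error rate is held.
- **That the trial falls short of its planned precision.** The 82% and 99% figures were set with baseline adjustment alone, and they reproduce.
- **That immunosuppressant use matters as much as duration.** Among patients on treatment in March 2020 it was nearly constant, and likely dose changes before the 3-month endpoint are an exclusion. The figure covers only 11 patients, but the article gives no other.

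**Conclusion.** This is a small, optional gain in efficiency. It is neither an error nor a contradiction, and not a threat to validity. Pre-specifying duration would add about 1 to 4 points of HAQ-DI power, equivalent to about 2 to 7 evaluable patients, if it explains 3% to 10% of the residual variance. The mRSS would gain the same only if its baseline correlation is near 0.6 rather than the database value of 0.9. The size rests entirely on the assumed R². The case for acting is that the payoff is lopsided: several points if duration is prognostic, less than 0.1 point lost if it is not. Additional strata are not warranted on this evidence.

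**What to change.** Add time since onset of skin involvement at baseline (in months, continuous), with its interaction with time point, as a fixed covariate in both primary mixed models. Keep the missingness-based rule as a separate provision.

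Date and document the choice before any comparison of outcomes by arm, including the planned interim futility analysis. That analysis needs about 30 participants with 3-month data, and the article reports 25 recruited. Waiting until database lock would be too late: 11 patients have been unblinded and the trial is moving to open label, so a late choice could be called data-driven.

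Omit immunosuppressant use from the primary models, or confine it to a sensitivity analysis. Leave eligibility and stratification unchanged.

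**Cost.** One amended sentence in the analysis plan; three fixed-effect parameters per model (one per time point), or about one degree of freedom per contrast; and a check that the onset date is recorded, since confirming a duration under 3 years needs only a threshold.

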### Outcome measures

Primary and secondary efficacy outcome measures, and safety measures, are shown
in Table 2.

**Table 2. table2-2397198320957552:** Efficacy outcome measures and safety measures.

Primary outcomes	Assessed at 3 months (Visit 4)	Functional ability as measured by the Health Assessment Questionnaire Disability Index (HAQ-DI)
		Modified Rodnan skin score (mRSS)
Secondary outcomes	Assessed at: 6 weeks (Visit 3) 3 months (Visit 4) 6 months (Visit 5)	HAQ-DI (6 weeks and 6 months)
		mRSS (6 weeks and 6 months)
		Perceived pain as measured by the HAQ Visual Analogue Scale (HAQ VAS)
		Multisystem effects of SSc as measured by the Scleroderma Health Assessment Questionnaire Visual Analogue Scales (SHAQ VAS)
		Functional ability as measured by the 11-point Scleroderma Functional Index (to complement the HAQ-DI)
		Scleroderma Skin Patient Reported Outcome (SSPRO)
		Pruritus as measured by the 5-D Itch Questionnaire
		Hand disability as measured by the Cochin Hand Function Scale (CHFS)
		Fatigue as measured by the Functional Assessment of Chronic Illness Therapy (FACIT) questionnaire
		Anxiety and depression as measured by the Hospital Anxiety and Depression Scale (HADS)
		Helplessness as measured by the 5-Item helplessness subscale of the Rheumatology Attitudes Index (RAI)
		Health status, mental and physical aspects, as measured by the Short Form (36) Health Survey v2^®^ (SF-36v2^®^)
		Health utility as measured by the EuroQoL (EQ-5D-3L)
		Patient and Physician Global Assessments
		Digital ulcer count
		Tendon friction rubs
		Joint count
Safety measures	Assessed at: 6 weeks (Visit 3) 3 months (Visit 4) 6 months (Visit 5)	Blood pressure
		Renal function as assessed by: Serum creatinine Estimated Glomerular Filtration Rate Urinary protein/creatinine ratio
		Full blood count
		Blood glucose

